**Table 6.1-4. Schedule of Events for Resistance Monitoring**

| Part 3: MAD HCV NS5b Resistance Monitoring |          |                  |            |
|--------------------------------------------|----------|------------------|------------|
| Assessments \ Day                          | Baseline | End of Treatment | Completion |
|                                            | 1        | 7                | 21 (±1)    |
| Resistance Testing                         | X        | X                | X          |

Sequencing of the HCV polymerase NS5b coding region will be conducted at baseline, end of treatment (Day 7; where HCV RNA levels > 1000 IU/mL) and at Day 21 for subjects with CHC enrolled in the study. Additional sequencing will be conducted in the following circumstances:

- HCV RNA rebound: defined as subjects who demonstrate a sustained  $\geq 1.0 \log_{10}$  IU/mL increase of HCV RNA above nadir before the end of treatment ( $\geq 2$  consecutive measurements), where nadir is a  $\geq 1.0 \log_{10}$  IU/mL decrease from baseline.
- Partial response: defined as those subjects who show an initial HCV RNA decline ( $\geq 1.0 \log_{10}$  IU/ml decrease from baseline) followed by stabilization ( $\geq 2$  consecutive measurements with HCV RNA levels similar to those at nadir) while receiving AL-335.

If a patient meets either of these definitions, then attempts will be made to determine the NS5B coding sequences for any samples with HCV RNA > 1000 IU/mL. Subsequently, phenotypic characterization of selected samples may be carried out by the amplification of the entire NS5b coding region and cloning into a replicon shuttle vector.

## 6.2 ON-STUDY EVALUATIONS, PROCEDURES, AND DOSING

Where multiple procedures are scheduled at the same time point(s) relative to dosing, the following chronology of events should be adhered to, where possible:

- Vital signs: obtain after ECGs and as close as possible to scheduled time, but prior to blood specimen collection.
- Blood pressure/pulse rate: obtain as close as possible to scheduled time, but prior to blood specimen collection.
- PK blood specimens: obtain at scheduled time.
- PK urine samples: subjects may void their bladder up to 10 minutes prior to dosing i.e., 0 hour.
- Assessments conducted within 10% of the nominal time (e.g., within 6 minutes of a 60 minute time point) from dosing will not be captured as a protocol deviation as long as the exact time of the assessment is noted on the source document and data collection record (e.g., CRF).
- Other Procedures: all other procedures should be obtained as close as possible to the scheduled time but may be obtained before or after blood specimen collection
- Where no scheduled time is specified a given evaluation can be conducted 2–4 hours postdosing.

### 6.2.1 Diet, Fluid, and Activity

While in the Phase 1 unit, subjects in Part 1–3 will receive standardized diets at scheduled times that do not conflict with study-related procedures. In Part 1, prior to each dose of study medication, subjects may fast from food for at least 8 hours overnight until 4 hours postdose (SAD Cohorts 1-5). For the Optional SAD Cohorts (6-8), prior to each dose of study medication subjects will receive a standard meal and 250 mL of water. In Part 2, subjects will receive a single dose in a fasted state (Cohort 3 from Part 1) followed by a single dose in a fed state after an 11- 21 day washout. Except as part of dose administration, water may be consumed freely except between 1 hour prior to dosing and 2 hours post-dosing. In Part 3, prior to each dose of study medication, subjects will receive a standard meal and 250 mL of water.

Subjects in Part 2, the food effect study phase, will be given a standardized high-fat content meal within 30 minutes of their second dose; the meal will be completed at least 10 minutes prior to dosing. The meal will consist of the following ([CDER Guidance, 2002](#)):

- Two eggs fried in butter
- Two strips of bacon
- Two slices of toast with butter
- Four ounces of hash brown potatoes (fried with butter)

- Eight ounces (240 mL) of whole milk

Subjects will refrain from any strenuous activities from 48 hours prior to check-in through study completion. Consumption of grapefruit or grapefruit products such as juice are prohibited during study participation. Other prohibited foods that either inhibit or induce the CYP450 enzyme class are included in [Appendix C](#).

### **6.2.2 Pharmacokinetic Blood and Urine Sampling**

Blood samples for PK analysis will be collected at the scheduled times via an indwelling catheter and/or direct venipuncture using 4-mL Vacutainer collection tubes containing sodium fluoride/potassium oxalate anticoagulant pre-spiked with dichlorvos to stabilize the AL-335 and metabolites post-sampling. Saline or heparin flushes may be used to maintain viability of indwelling catheters. Additional information may be found in the Pharmacokinetic Sample Processing Manual.

Urine samples will be collected at the designated time points and processed according to the methodology described in the Laboratory Manual.

Samples may be used for future metabolite identification and/or further evaluation of the bioanalytical method. These data will be used for internal exploratory purposes and will not be included in the clinical study report.

Processing and shipping instructions are detailed in the Laboratory Manual. Plasma and urinary concentrations of AL-335, AL-022399 and AL-02227 will be determined by Inventiv Health Clinical Laboratories using a validated bioanalytical method.

All efforts will be made to obtain the PK samples at the exact nominal time relative to dosing. However, samples obtained within 10% of the nominal time (e.g., within 6 minutes of a 60 minute time point) from dosing will not be captured as a protocol deviation as long as the exact time of the sample collection is noted on the source document and data collection record (e.g., CRF).

To maintain the study blind, results of the individual PK analyses will not be shared with the Principal Investigator or Sponsor representatives involved in managing the study. PK data will be provided in a blinded fashion to the PI and Sponsor representatives to assist with dose escalation decisions during the course of the study.

### **6.2.3 Central Laboratory Evaluations**

Local laboratories will be used for all routine screening and study related laboratory evaluations. A central laboratory will be used to conduct IL-28B, and HCV RNA evaluations.

### **6.2.4 HCV Evaluations**

HCV RNA concentrations will be determined using COBAS® TaqMan® HCV Test (Version 2.0, Roche). To maintain the study blind, results of the individual HCV viral load analyses will not be shared with the PI or Sponsor representatives involved in managing the study.

### 6.2.5 HCV Resistance Monitoring

Blood taken for monitoring of potential viral resistance to AL-335 will be evaluated by the sponsor or designee by population sequencing of the HCV polymerase NS5B coding region and phenotypic susceptibility testing. Clonal sequencing, Next-generation sequencing, and/or sequencing of other regions of the HCV genome may also be performed. For all subjects with CHC, samples for viral resistance testing will be taken at the same time points as those taken for HCV RNA evaluation (see [Table 6.1-3](#)). Samples for viral resistance monitoring will be selected based on the results obtained from the HCV RNA determinations. Samples encompassing the NS5B region or other regions of the HCV genome may also be used in further phenotypic studies.

Further details of HCV resistance monitoring procedures can be found in [Table 6.1-4](#).

Approximately 8mL of blood will be collected at each protocol-specified time point using an indwelling venous catheter and/or direct venipuncture into two 4mL (plastic) K2EDTA Vacutainer tubes. Additional processing information may be found in the Laboratory Manual.

### 6.2.6 12-Lead Electrocardiograms

The investigator will be responsible for evaluating the results and determining if any findings are of clinical significance. ECGs will be obtained in a semi-recumbent or recumbent position after 5 minutes of rest and may be repeated at the investigator discretion to account for erroneous readings.

### 6.2.7 Vital Signs

Vital signs (oral or body temperature, respiratory rate, and automated supine blood pressure and heart rate) will be obtained in a semi-recumbent or recumbent position after 5 minutes of rest. Blood draws will take precedence over vital signs in the event that the two procedures need to be conducted at the same time. In this case, vital signs should be obtained as close the scheduled time as possible, after ECG assessments and prior to blood collections.

### 6.2.8 Physical Examinations

Subjects will have complete physical examination at screening and study completion. A brief symptom directed examination will be conducted at all other timepoints as indicated in the Schedule of Events. BMI will be calculated by clinic staff at the Screening visit using the following formula:

$$\text{BMI} = \text{weight in kg} \div (\text{height in meters})^2$$

### 6.2.9 Contraception

Males will either be sterile or agree to one of the following methods of contraception from first dose of study drug until 90 days following the final dose of study drug:

- Male condom with spermicide  
A sterile sexual partner

Males will advise their female sexual partners to use:

- A non-hormonal IUD with spermicide
- Female condom with spermicide
- Contraceptive sponge with spermicide
- Diaphragm with spermicide
- Cervical cap with spermicide
- Oral, implantable, transdermal, or injectable contraceptives

For all subjects, two forms of contraception should be employed.

## **7.0      SAFETY MONITORING AND REPORTING**

### **7.1      DEFINITIONS**

#### **7.1.1      Pretreatment Events**

A pretreatment event is any event that meets the criteria for an AE/SAE and occurs after the subject signs the informed consent form but before receiving the first administration of study drug.

#### **7.1.2      Adverse Events**

An AE is any event, side effect, or untoward medical occurrence in a subject enrolled in a clinical trial whether or not it is considered to have a causal relationship to the study drug. An AE can therefore be any unfavorable and unintended sign, symptom, laboratory finding outside of normal range with associated clinical symptoms or suspected latent clinical symptoms in the opinion of the investigator, physical examination finding, or disease temporally associated with the use of the study drug, whether or not the event is considered related to the study drug.

Planned hospital admissions or surgical procedures for an illness or disease that existed before the subject was enrolled in the study are not to be considered AEs unless the condition deteriorated in an unexpected manner during the study (e.g., surgery was performed earlier than planned).

#### **7.1.3      Serious Adverse Events**

A Serious Adverse Event (SAE) is any untoward medical occurrence at any dose that:

- Results in death: This includes deaths that appear to be completely unrelated to study medication (e.g., a car accident).
- Is a life-threatening event: An event that places the subject at immediate risk of

death at the time of the event; it does not refer to an event that hypothetically might have caused death if it were more severe.

- Requires inpatient hospitalization or prolonged hospitalization of an existing hospitalization.
- Results in permanent or prolonged (at least 28 days in duration) disability or incapacity.
- Is a congenital anomaly or birth defect in the offspring of a study subject.
- Medically important event: An event that may not be immediately life-threatening, or result in death or hospitalization, or require intervention to prevent one of the outcomes listed above, but is considered medically significant for other reasons. An opportunistic or otherwise unusual infection for the investigator's practice, such as tuberculosis, will be considered medically significant.

The term severe is used to describe the intensity of a specific event (as in mild, moderate, or severe); the event itself, however, may be of minor medical significance (such as severe headache). This is not the same as serious, which is based on outcome of the event, as described above. Seriousness, not intensity, serves as a guide for defining regulatory reporting obligations.

## **7.2 DOCUMENTING AND REPORTING OF ADVERSE EVENTS (INCLUDING SERIOUS ADVERSE EVENTS)**

Adverse Events will be evaluated and documented using the grading scales contained in the Division of AIDS Table for Grading the Severity of Adult and Pediatric AEs (December 2004) and shown in [Appendix E](#).

### **7.2.1 Documenting and Reporting Pretreatment Events**

For enrolled subjects, record all pretreatment AEs that occur after the subject signs the informed consent form but before the first study drug administration on the AE CRF and Clinical Trials SAE Form (if applicable). The AE CRF and SAE form will indicate that the event occurred prior to the first dose of study drug.

### **7.2.2 Documenting and Reporting Adverse Events**

**Record all AEs** that occur from Day 1 (from start of study medication administration) to the follow-up visit, regardless of the intensity, seriousness, or relationship to study drug, on the AE CRF, for all enrolled subject. Subjects who do not enroll (i.e., screen failures), collect AEs until the time of screen failure.

Grade AEs (serious and nonserious) in accordance with the scale presented below:

- Mild adverse event (minor; no specific medical intervention; asymptomatic laboratory findings only;; marginal clinical relevance); does not interfere with regular activities

- Moderate adverse event (minimal intervention; local intervention; noninvasive intervention [packing, cautery]); moderate level of discomfort and significantly interferes with regular activities
- Severe and undesirable adverse event (significant symptoms requiring hospitalization or invasive intervention; transfusion; elective interventional radiological procedure; therapeutic endoscopy or operation); significant level of discomfort and prevents regular activities
- Life-threatening or disabling adverse event (complicated by acute, life-threatening metabolic or cardiovascular complications such as circulatory failure, hemorrhage, sepsis. Life-threatening physiologic consequences; need for intensive care or emergent invasive procedure; emergent interventional radiological procedure, therapeutic endoscopy or operation).

Once an event has resolved, any recurrence will be reported as a new event with a corresponding grade.

Whenever possible, report AEs as a specific diagnosis or syndrome (e.g., flu syndrome) rather than as individual signs or symptoms. If no specific diagnosis or syndrome is identified, AEs should be reported as separate and individual events.

An AE includes the following:

- Pre-existing event that increases in frequency or intensity.
- Condition detected or diagnosed during the study period, even though it may have been present, in retrospect, prior to the first dose of study drug.
- Laboratory abnormalities outside of normal limits and requiring therapeutic intervention.
- An overdose of the study drug without any signs or symptoms will be considered an AE. A calculated dose that exceeds its correct dose by 10% or more and is administered to the subject will be considered an overdose and documented as an AE.

The following events **will not** be identified as AEs in this study:

- Progression or exacerbation of the subject's underlying disease. However, clinical sequelae that result from disease progression, such as pleural effusion or small bowel obstruction, are reportable as AEs.
- Medical or surgical procedures (e.g., surgery, endoscopy, tooth extraction, etc); however, the condition (the "triggering event") that leads to the procedure may be an AE.
- Pre-existing conditions present or detected prior to the first dose of study drug that do not worsen.

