All 8 healthy volunteers or 8 of the 10 subjects with CHC in each cohort must complete the dosing schedule before a decision is made to proceed to subsequent dosing cohorts. Additional subjects may be recruited to evaluate a dose further if the data obtained from the initial cohort is not sufficiently robust for any given dose level. A decision to replace subjects for reasons other than safety-related will be made by the Sponsor in consultation with the PI.

Dose escalation will be suspended:

- If 4 or more subjects in a dose cohort experience moderate AEs or toxicities considered possibly or probably related to study drug, OR
- If 2 or more subjects in a dose cohort experience severe AEs or toxicities considered possibly or probably related to study drug, OR

- If one or more subjects in a dose cohort experience life threatening AEs or toxicities considered possibly or probably related to study drug. In this case, the Sponsor's Medical Monitor will review the treatment allocation to determine if the subject is receiving study medication or placebo. If the subject was receiving placebo then dose escalation may recommence, OR
- If 3 or more subjects in a dose cohort experience a sustained QTcF greater than 500 msec associated with an increase greater than 60 msec , OR
- If 3 or more subjects in a dose cohort experience a sustained resting heart rate of greater than 100 beats per minute

If dose escalation is suspended, a more comprehensive review of the safety data will be undertaken by the Sponsor and the PI. Based on this review, a decision will be made to continue with dose escalation, repeat a previously evaluated dose, evaluate a lower dose, modify the protocol, or terminate the study.

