| IL28B determination                                          |           | 3        |    |        |    |    |    |    |    |    |    |           |    |    |    |    |            |
| PK Samples                                                   |           |          |    | 40     | 4  | 4  | 4  | 4  | 4  | 40 | 8  | 4         | 4  | 4  | 4  | 4  | 4          |
| Liver Function Tests                                         |           | 2        | 2  | 2      | 2  | 2  | 2  | 2  | 2  | 2  | 2  | 2         | 2  | 2  | 2  | 2  | 2          |
| CBC w/diff PT/PTT & INR and Urinalysis, Serum Chemistry      | 15        | 15       |    |        | 15 |    |    |    |    | 15 |    | 15        |    |    | 15 |    | 15         |
| HCV RNA concentration                                        | 6         | 6        |    | 24     | 6  | 6  | 6  | 6  | 6  | 6  | 6  | 6         | 6  | 6  | 6  | 6  | 6          |
| Plasma for drug resistance monitoring                        |           | 8        |    | 8      | 8  | 8  | 8  | 8  | 8  | 8  | 8  | 8         | 8  | 8  | 8  | 8  | 8          |
| Pregnancy Test                                               | 2         | 2        |    |        |    |    |    |    |    |    |    | 2         |    |    |    |    | 2          |
| Alpha-fetoprotein                                            | 7         |          |    |        |    |    |    |    |    |    |    |           |    |    |    |    |            |
| Totals                                                       | 43        | 38       | 2  | 74     | 35 | 20 | 20 | 20 | 20 | 71 | 24 | 37        | 20 | 20 | 35 | 20 | 37         |

Estimated total volume is ~ 536 mL. Note that volumes are approximate. There may be some variation in the volumes that are required between laboratories at different clinical trial centers.

**Appendix E. Toxicity Tables****DIVISION OF AIDS TABLE FOR GRADING THE SEVERITY OF ADULT AND PEDIATRIC ADVERSE EVENTS. PUBLISH DATE: DECEMBER, 2004****Quick Reference**

The Division of AIDS Table for Grading the Severity of Adult and Pediatric AEs (“DAIDS grading table”) is a descriptive terminology to be utilized for AE reporting in this study. A grading (severity) scale is provided for each AE term.

**General Instructions***Estimating Severity Grade*

If the need arises to grade a clinical AE that is not identified in the DAIDS grading table, use the category “Estimating Severity Grade” located at the top of the table on the following page.

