| PARAMETER                                                   | GRADE 1
MILD                                                                          | GRADE 2
MODERATE                                                                                          | GRADE 3
SEVERE                                                                                         | GRADE 4
POTENTIALLY
LIFE-THREATENING                                                                  |
| Prolonged QTc                                               |                                                                                          |                                                                                                              |                                                                                                           |                                                                                                             |
| Adult > 16 years                                  | Asymptomatic, QTc interval 0.45 – 0.47 s OR Increase in interval < 0.03 s above baseline | Asymptomatic, QTc interval 0.48 – 0.49 s OR Increase in interval 0.03 – 0.05 s above baseline                | Asymptomatic, QTc interval $\geq 0.50$ s OR Increase in interval $\geq 0.06$ s above baseline             | Life-threatening consequences, e.g., Torsade de pointes or other associated serious ventricular dysrhythmia |
| Pediatric <math>\leq 16</math> years                 | Asymptomatic, QTc interval 0.450 – 0.464 s                                               | Asymptomatic, QTc interval 0.465 – 0.479 s                                                                   | Asymptomatic, QTc interval $\geq 0.480$ s                                                                 | Life-threatening consequences, e.g., Torsade de pointes or other associated serious ventricular dysrhythmia |
| Thrombosis/embolism                                         | NA                                                                                       | Deep vein thrombosis AND No intervention indicated (e.g., anticoagulation, lysis filter, invasive procedure) | Deep vein thrombosis AND Intervention indicated (e.g., anticoagulation, lysis filter, invasive procedure) | Embolic event (e.g., pulmonary embolism, life-threatening thrombus)                                         |

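### Adverse events are to be graded on two different severity scales, and the dose-escalation suspension rule does not say which one it counts

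*Protocol*

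**What the plan says.** Section 7.2 opens with "Adverse Events will be evaluated and documented using the grading scales contained in the Division of AIDS Table", which Appendix E reproduces. Appendix E repeats that the table "is a descriptive terminology to be utilized for AE reporting in this study".

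Section 7.2.2 then gives the investigator a second instruction, "Grade AEs (serious and nonserious) in accordance with the scale presented below", followed by a four-level scale defined largely by the intervention needed and the effect on daily activity. Its lowest level begins "Mild adverse event (minor; no specific medical intervention; asymptomatic laboratory findings only". Its third level begins "Severe and undesirable adverse event (significant symptoms requiring hospitalization or invasive intervention". Neither section refers to the other.

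Section 5.1.1 makes suspension of dose escalation mandatory when any of five limbs is met. Three depend on severity, for events judged possibly or probably related: four or more subjects with moderate events, two or more with severe events, or one or more with a life-threatening event. The severe limb reads "If 2 or more subjects in a dose cohort experience severe AEs or toxicities considered possibly or probably related to study drug". None of the three names a grading scale. The other two limbs are numerical (heart rate and QTcF). The QTcF limb is "If 3 or more subjects in a dose cohort experience a sustained QTcF greater than 500 msec associated with an increase greater than 60 msec".

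**The concern.** Both grading instructions are current text and cover the same events. An investigator who follows 7.2 and one who follows 7.2.2 can give the same event different grades, and both comply with the protocol. The suspension rule counts subjects by grade in cohorts of 8 (Part 1) or 10 (Part 3), so a one-level difference can decide whether the rule is met.

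This is a first-in-human study with a compulsory rule, planned at up to 6 sites in four countries. If sites followed different sections, inconsistent grades would enter one cohort count. The same grades feed the adverse-event data that form part of the primary endpoint. An analysis plan cannot repair this, because grading and escalation decisions are made while the study runs.

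**Working it through.** The protocol gives no operating characteristics for the suspension rule, so there is no figure to reproduce. The check is to grade the same event on each scale and read off the number of subjects that 5.1.1 then requires.

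**Inputs.** Limbs from 5.1.1: moderate at 4 subjects, severe at 2, life-threatening at 1. Grades from Appendix E (1 mild, 2 moderate, 3 severe, 4 potentially life-threatening) and from the 7.2.2 list. Each event is taken as possibly related, with no other counted event in the cohort.

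| Event | Appendix E | Subjects to suspend | 7.2.2 | Subjects to suspend |
|---|---|---|---|---|
| Generalized urticaria, oral treatment, no hospitalization | Grade 3 (allergic reaction row) | 2 | Can be moderate: no hospital care or invasive procedure | 4 |
| Headache, hospitalization indicated, not life-threatening | Grade 4 (headache row) | 1 | Severe: hospitalization sits at that level | 2 |
| Fever 39.4 to 40.5°C, managed outside hospital | Grade 3 by temperature alone | 2 | No temperature criterion; can be moderate | 4 |

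For urticaria and fever the scales therefore disagree at 2 or 3 affected subjects. For headache they disagree at exactly 1.

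**Illustration with assumed rates.** Let p be the chance that a subject has a related event that is severe in Appendix E and moderate in 7.2.2. The documents give no value for p. With subjects independent and p the same for everyone in the cohort, the chance of suspension is the binomial probability of at least 2 subjects (Appendix E) or at least 4 (7.2.2):

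| p | n=8: at least 2 | n=8: at least 4 | n=10: at least 2 | n=10: at least 4 |
|---|---|---|---|---|
| 0.05 | 0.057 | <0.001 | 0.086 | 0.001 |
| 0.10 | 0.187 | 0.005 | 0.264 | 0.013 |
| 0.20 | 0.497 | 0.056 | 0.624 | 0.121 |
| 0.30 | 0.745 | 0.194 | 0.851 | 0.350 |

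**Asymptomatic QTc prolongation.** Grade 3 in Appendix E is "Asymptomatic, QTc interval $\geq 0.50$ s OR Increase in interval $\geq 0.06$ s above baseline". Take QTcF rising from 440 to 510 msec: the rise is 510 − 440 = 70 msec (0.07 s) and the value is 0.51 s, so it is Grade 3 on both criteria. If it counts as a related event, two such subjects meet the severe limb, whereas the dedicated QTcF limb needs three. Take 410 to 475 msec: the rise is 65 msec (0.065 s), so it is Grade 3, but 475 never exceeds 500 and the dedicated limb cannot be met. The 7.2.2 grade of either finding is a matter of judgement, so no count is given for that scale. The comparison does show that the severity limbs and the QTcF limb overlap once Appendix E is adopted.

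**Whether other text resolves the conflict.** The 7.2.2 scale is not a fallback for unlisted events, because Appendix E has its own row for those. The Appendix E instruction to take the higher of two grades applies to an event lying between two grades of that table; it does not rank the table against another scale.

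**The case against.** The strongest reply is that 5.1.1 counts adverse events or toxicities. Appendix E is titled Toxicity Tables, so an Appendix E Grade 3 finding might satisfy the severe limb as a toxicity whatever its 7.2.2 grade. This is a natural reading and probably what was meant. But 5.1.1 neither defines toxicity nor cites Appendix E, so it remains an inference. It supports the choice of scale for the fix without making the present text clear.

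A reader might infer something stronger: that under 7.2.2 an asymptomatic laboratory abnormality, such as lipase at 4 or 6 times ULN, is always mild and can never suspend escalation. The documents do not support that. Section 7.1.2 makes a laboratory finding an adverse event only with clinical symptoms, or with latent ones suspected by the investigator. Section 7.2.2 adds abnormalities that need treatment. An untreated, asymptomatic lipase rise would generally not be an adverse event, and could enter 5.1.1 only as a toxicity, which points to Appendix E. Nor is an asymptomatic QTcF rise forced into mild, since an ECG finding is not a laboratory finding and the mild entry also describes minor events of little clinical relevance. No fixed range of subject counts should be claimed for such findings.

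Two further points stand. The scales agree for some symptomatic events, because 7.2.2 also treats loss of regular activities as severe, close to the Appendix E functional criterion; the urticaria and fever examples assume this is absent. And the consequence is bounded: the sponsor, with the investigator, reviews each cohort's safety data regardless, and suspension leads to a review that may end in continuing.

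**Conclusion.** The contradiction is real and reaches a mandatory safety rule. For clear clinical events it shifts the trigger from 2 subjects to 4 (urticaria, fever) or from 1 to 2 (headache), so the severe and life-threatening limbs are both affected. This rests on the events being judged possibly related, on no other counted events in the cohort, on Appendix E Grade 4 being read as life-threatening, and, for urticaria and fever, on regular activities not being prevented.

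The effect is confined to the formal trigger. A reader might infer that escalation could go ahead without safety review, or that sites are known to grade differently; the protocol supports neither. Section 1.1 reports no SAEs and no clinically relevant laboratory or ECG signal in 40 healthy volunteers given single doses up to 1200 mg or two 400 mg doses, so the rule matters mainly for repeat dosing in Part 3. The protocol should be corrected, but the defect does not undermine the design.

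**What to change.** - In 5.1.1, state that moderate, severe and life-threatening mean Appendix E Grades 2, 3 and 4.
- Delete the four-level scale in 7.2.2 and refer to Appendix E, which already covers unlisted clinical events.
- Align the severity field on the CRF to Grades 1 to 4.
- In 5.1.1, state whether asymptomatic QTc prolongation is judged only by the dedicated QTcF limb or also by the severity limbs. Otherwise two related rises of at least 0.06 s could suspend escalation before the three-subject QTcF limb applies.

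The cost is a short amendment, a CRF change and a note to sites. The downside is a possibly earlier pause for review, because Appendix E grades some findings higher. For example, four subjects with related QTc increases of 0.03 to 0.05 s would meet the moderate limb unless QTc is reserved to its own limb, and one related lipase above 5 times ULN would be Grade 4. The sponsor should accept these consequences knowingly or write explicit exceptions.
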